### Sample size

Taking into account that until 50% infarct size is due to reperfusion damage, a minimal efficacy of the intervention is considered to reach a relative improvement up to 25% infarct size. Similar studies applying the same method have provided the accuracy of measurements as variance value. The sample size was calculated from the following formula [76]:

$$n=2{\left(\mathrm{ZS}+\mathrm{ZP}\right)}^{2}x\;S^{2}/{\left(\mathrm{MA}–\mathrm{MB}\right)}^{2}$$

Where *n* is the sample size for each group, “ZS” corresponds to the level of significance (5%), “ZP” represents the potency (80%), “MA” is the mean of supplemented group,MB, the mean of the placebo group (control), and S is the variance of CMR determination for assessment for IS. A 10% patient loss was considered for the purposes of this calculation. This calculation rendered a sample size of 66 patients for each branch (placebo and supplemented). This sample size is suitable to be covered by the population of patients being treated for PCA in the Cardiovascular Department, University of Chile Clinical Hospital, and Cardiovascular Center, San Borja Arriarán Clinical Hospital, during the estimated period (3 years).

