### Statistical analyses

Results of continuous variables will be expressed as mean ± standard deviation (SD). Comparison between parametric variables will be performed by using Student *t* test for unpaired samples. Nonparametric variables will be expressed as median (interquartile range) and compared through Wilcoxonrank-sum test. The significant differences for normally distributed variables will be compared with Student *t* test analysis of variance (ANOVA) for repeated measures. The significant differences for non-normally distributed variables will be compared by using the Mann–Whitney *U* test. Categoric variables will be expressed as numbers and frequencies (percentage). The Fisher Exact test with Katz approximation will be used to compare adverse-event frequencies.

Determination and data obtained for infarct size and ventricular function by cardiac resonance will be evaluated by two independent individuals with the purpose of applying the concordance kappa index. Among the limitations of using infarct size as an outcome, is that the use of final infarct size carries the risk of imbalances in baseline myocardium at risk, according to treatment group, as well as comparing different AMI locations, which may have different sensitivity to the therapy [80].

In addition to this, the groups may have variable time to reperfusion and other confounding variables that determine infarct size [81,82]. Whereas some of these difficulties may have been corrected through a careful stratification on entering the study, this option was discarded, given the small sample size of this study. We are currently considering an analysis of the data though a linear regression model, adjusted by all confounding variables, such as those mentioned before, and others present in the current literature [83]. *P*< 0.05 will be considered statistically significant. Results will be analyzed by using Stata version 8.0, Microsoft Excel,and Graphpad Prism 4.0.

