### Trial management

Patients or their representatives will be asked to sign two copies of the informed consent. Patients will be given a copy of their consent form to keep for reference, and the other will be filed in the Investigator Site File on site. Data forms will be checked for completeness and merged into a master chart, which will be communicated to the study statistician. Patient confidentiality will be maintained at every stage.

Patients may withdraw from the trial or the trial treatment at any time without prejudice. Patients may be withdrawn from the study at the discretion of the local ethics committee for safety reasons. All adverse events and serious adverse events will be recorded during hospital stay and through patient communication while they are being subjected to ambulatory oral treatment. The study coordinator will conduct meetings with the study statistician on a regular basis, and the Chief Investigator will be made aware of all adverse events and serious adverse events as they happen.

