## Discussion

Given the unpredictable nature of AMI, it is not feasible to obtain a basal myocardial image of patients; however, this trial also does not include performing an “acute” imaging on admission before the PCA (again, for feasibility reasons), but rather relies on performing a CMR on the sixth day after AMI. In this context, it is impossible to distinguish reperfusion damage from ischemic damage in the same patient, based in a single “6-day after” cardiac image. It would be expected on an imaging comparison among groups that on the 6^th^ and 84^th^ days, the placebo group exhibits, on average, a greater infarct size compared with the supplemented group. Any significant reduction of infarct size in the supplemented group could be attributed only to a decrease of reperfusion damage, because full coronary ischemia would not allow the arrival of ascorbate to the postoccluded artery segment. However, it will be impossible to determine whether a significant decrease of infarct size corresponds to total or partial reduction reperfusion damage.

To the best of our knowledge, no published reports have assessed human populations with high vitamin C levels in AMI patients during the PCA procedure; therefore, it is more difficult to compare data obtained with those in the current literature. In addition, given the characteristics of the study population, trial results are not applicable to patients having a second AMI, III or IV Killip score AMI, or other conditions established in the trial-exclusion criteria. Given that this study is being performed in a mostly Chilean population, its applicability to other ethnicities is uncertain.

Concerning the loss of data or patients during the study, patients undergoing a claustrophobic reaction will not be capable of being analyzed by CMR. Furthermore, due to the ambulatory nature of the trial, a small loss of patients may occur between the day 6 CMR and day 84 CMR. Given the multicentric nature of the study, the loss of samples is possible.

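### At day 84 the named two-sample tests compare completers only, so selective loss after the day-6 scan could bias that comparison although the day-6 scans could correct it

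*Protocol article*

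**What the plan says.** - **Outcome.** Under Primary and secondary outcomes, the primary outcome is infarct size by CMR at both day 6 and day 84 after angioplasty.
- **Expected loss.** The Discussion says that "a small loss of patients may occur between the day 6 CMR and day 84 CMR", and that patients with claustrophobia cannot be scanned. Under Sample size, "A 10% patient loss was considered for the purposes of this calculation".
- **Tests.** Statistical analyses names the unpaired Student t test, Wilcoxon rank-sum or Mann–Whitney tests, and "analysis of variance (ANOVA) for repeated measures". An adjusted linear regression is only under consideration. No test is tied specifically to infarct size.
- **Withdrawal.** Under Trial management, one sentence lets patients leave either the trial or only its treatment. The next reads: "Patients may be withdrawn from the study at the discretion of the local ethics committee for safety reasons". It does not say whether the scheduled scans are still done.
- **Reporting.** Randomization and followup promises the reasons for losses after randomisation.

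**The concern.** A two-sample test on day-84 infarct size compares the patients who came back for the second scan. If patients with large infarcts leave more often in one arm, the groups compared are no longer the groups randomised. Losing large infarcts from the placebo arm would mask a benefit; losing them from the vitamin arm would exaggerate or create one. Most patients who leave between the scans will have a day-6 infarct size on file, which is the best available predictor of the missing value, yet these tests cannot use it at day 84. Inflating the sample size replaces the lost numbers but does not restore the balance.

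**Working it through.** **Inputs from the article.** 5% significance (sidedness not stated; two-sided used here), 80% power, 10% loss, 66 per arm. The target is that "a minimal efficacy of the intervention is considered to reach a relative improvement up to 25% infarct size".

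**Assumptions, not in the article.** Day-6 to day-84 correlation ρ of 0.7 to 0.9; the whole 10% loss falling after day 6; loss depending on day-6 size; normal data.

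**1. The plan's own figure.** The formula is n = 2(ZS + ZP)² S² / (MA − MB)². No values are given for MA, MB or S, so 66 cannot be reproduced. Working backwards, 66 × 0.9 = 59.4 evaluable per arm (equally, 60 × 1.1 = 66). The implied detectable difference is (1.96 + 0.84) × √(2/60) = 0.51 SD. For a 25% reduction this means SD / control mean of about 0.25 / 0.51 = 0.49.

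**2. What the 10% allowance does.** At that effect, power is 0.84 with 66 per arm, 0.797 with 59 and 0.754 with 53. The planned loss leaves power at about 80%. None of this bears on who is lost.

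**3. What each named test can use at day 84.**
- Unpaired t or rank test: day-84 scans only.
- Repeated-measures ANOVA: complete pairs only if fitted to complete cases. Some fits keep incomplete patients, and the article does not say which is meant.

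**4. Bias of the completer comparison.** Let δ be the shift, in SD, in an arm's mean day-6 size caused by losing some patients. When loss depends on day-6 size only, the day-84 completer mean shifts by ρδ, so

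bias = ρ(δ_vitamin − δ_placebo).

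Equal shifts cancel. At the bound, one arm loses exactly its largest 10% and the other loses 10% at random. The shift is then −φ(1.28)/0.9 = −0.195 SD on the day-6 scale. Multiplied by 0.7, 0.8 and 0.9 this gives 0.137, 0.156 and 0.176 SD in size. Simulation with 66 per arm and no true effect (20,000 trials per scenario) agrees:

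| Loss after day 6, 10% per arm | Bias, ρ = 0.7 / 0.8 / 0.9 (SD) | Share of 0.51 SD | False-positive rate |
|---|---|---|---|
| Similar relation to size in both arms | about 0 (checked at ρ = 0.85) | about 0 | about 5% |
| One arm only, log-odds of loss up 1.0 per SD of day-6 size | 0.060 / 0.069 / 0.079 | 12–16% | 6–7% |
| Bound: one arm loses its largest infarcts | 0.139 / 0.162 / 0.180 | 27–35% | 12–19% (13–20% on rerun) |

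A separate large-sample run at ρ = 0.85 gave 0.076 to 0.080 SD for the one-arm case, in either direction. Unequal rates (15% against 5%) with the same dependence in both arms gave 0.071 to 0.075 SD. A steeper one-arm dependence (2.0 per SD) gave 0.12 SD.

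**5. An estimator using both scans.** Its bias was about 0 in every scenario, with a false-positive rate of 5 to 5.5% in the 66-per-arm simulation. Under purely random loss the day-84 variance fell from 0.0335 to 0.0318 (ρ = 0.7), 0.0332 to 0.0307 (ρ = 0.8) and 0.0347 to 0.0319 (ρ = 0.9), that is by about 5 to 8%.

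**The case against.** The strongest reply is that this is a condensed article. Rules for missing scans, death before a scan and analysis populations commonly sit in a full protocol or SAP that is not shown, and Statistical analyses never says that patients without a day-84 scan are excluded. That stands: a missing scoring rule is not the point here. What remains is that the article does name tests, and two of the three kinds cannot use an earlier scan at day 84 however they are applied.

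Several stronger readings are tempting but unsupported:

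- **That lost patients have no infarct-size result, or that day-6 data go unused.** Day 6 is itself a primary time point, and these patients count in that comparison. Only the use of their day-6 scan to inform day 84 is absent.
- **That repeated-measures ANOVA drops them from both days.** That depends on how it is fitted, which the article does not settle.
- **That deaths distort the result.** No section discusses death before a scan, and the 10% allowance is not broken down by cause. Claustrophobia, a cause the Discussion does name, has no obvious link to arm or infarct size.
- **That a safety withdrawal removes the day-84 scan.** Trial management does not say that scans stop. It leaves the matter unclear.

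The large figures are also open to challenge. They place all the loss after day 6, although the Discussion expects that loss to be small, and they need one arm to lose its very largest infarcts. The near-zero bias of the two-scan estimator is partly built in, because the simulated loss depends only on the observed day-6 value. Both criticisms are fair, so the figures are bounds and illustrations, not forecasts.

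**Conclusion.** The point holds for the day-84 comparison made with the unpaired t or rank tests, and for repeated-measures ANOVA if fitted to complete cases. The 10% allowance does not answer it. Bias is about zero when loss relates to infarct size alike and at the same rate in both arms. It is 0.06 to 0.08 SD, with a false-positive rate of 6 to 7%, when one arm moderately tends to lose larger infarcts. It is at most 0.14 to 0.18 SD, with about 12 to 20%, in the extreme bound. These sizes rest on the assumed correlations and loss patterns and are set against a design effect of about 0.51 SD. A reader might infer that the trial's false-positive rate is 12 to 20%; the article gives no loss pattern that would support this. The case for change is that a better use of scans already scheduled costs little and gains some precision even when loss is harmless.

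**What to change.** 1. **Analysis.** Replace the separate tests for infarct size with one likelihood-based mixed model of the day-6 and day-84 values (arm by day, centre, unstructured covariance), including every randomised patient with at least one CMR. Report the arm difference at each day.
2. **Reporting.** Give losses by arm as well as by reason; the reasons are already promised.
3. **Trial management.** Reconcile the two withdrawal sentences so that it is clear whether the scheduled CMRs are still obtained, with consent, after a safety withdrawal. This concerns data collection only; it takes no position on when treatment should stop.

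The cost is a few sentences, with no extra patients and no scans beyond those scheduled. The downside is that the model assumes loss after day 6 is explained by arm and the day-6 value. It does not address death or loss before day 6, including patients who cannot be scanned at all.

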## Trial status

The PREVEC trial began recruitment in February 2013. Forty-three patients have been enrolled to date (3 June 2014) The trial is scheduled to end in March 2016.

## Abbreviations

AMI: Acute myocardial infarction; CMR: cardiac magnetic resonance; eNOS: endothelial nitric oxide synthase; IL-1β: interleukin-1β; IL-6: interleukin-6; MDA: malondialdehyde; MAPK: mitogen-activated protein kinase; NO: nitric oxide; PCA: percutaneous coronary angioplasty; ROS: reactive oxygen species; SOD: superoxide dismutase; STEMI: ST-segment elevation myocardial infarction; TNF-α: tumor necrosis factor-α.
